## Abstract

**Background:**

This protocol is for a feasibility study of a mindfulness-based stress reduction (MBSR) program adapted for pregnant women with psychosocial vulnerabilities. The rationale for the study is the need for a wider array of evidence-based options to address prenatal mental health care needs in pregnant women. MBSR is a promising mental health intervention but has not yet been adapted for pregnant women with the aim of addressing prenatal mental health. The purpose is thus to evaluate the feasibility, acceptability, and clinical outcomes of an adapted MBSR program, prenatal MBSR, compared to usual care to inform a randomized controlled trial.

**Methods/design:**

Pregnant women (n = 60) referred to an outpatient clinic at Copenhagen University Hospital, Amager and Hvidovre, Denmark, will be recruited for the study. The design is a single-center feasibility trial, with prenatal MBSR, as an add-on to usual care. The primary outcome is to assess the feasibility of a full-scale randomized controlled trial. The secondary feasibility outcome includes possible effects of the adapted MBSR program estimated by self-report questionnaires measuring stress, anxiety, depression, well-being, decentering, reflective functioning, mindfulness, and compassion. Participants will be randomized in a 1:1 ratio to prenatal MBSR or usual care.

**Discussion:**

The study is part of the *Good Start to Family Life* study anchored at Copenhagen University Hospital, Amager and Hvidovre, Denmark. Teaching the skills of mindfulness meditation to a psychosocially vulnerable group of pregnant women could prove a viable and non-pharmacological approach to reduce stress, improve mental health, and provide support in the transition to parenthood. The outcomes of the feasibility study will inform the design of a fully powered randomized controlled trial.

**Trial registration:**

ClinicalTrials.gov, NCT04571190. Registered on September 30, 2020

**Supplementary Information:**

The online version contains supplementary material available at 10.1186/s40814-021-00860-w.

## Background

This protocol is for a feasibility study of an adapted mindfulness-based stress reduction (MBSR) program for psychosocially vulnerable pregnant women referred to a hospital-based outpatient clinic specialized in antenatal care. Reasons for referral to the outpatient clinic are mental disorders, substance abuse, or other psychosocial vulnerabilities such as domestic violence or a history of sexual abuse. The protocol is part of the *Good Start to Family Life* study, and the primary aim is to address the need of psychosocially vulnerable pregnant women and care providers. This in order to provide a wider array of evidence-based and non-pharmacological options to improve prenatal mental health. Mindfulness-based interventions are promising non-pharmacological interventions for mental disorders or symptoms, and performance has been found to be equivalent to evidence-based treatments, such as cognitive behavioral therapy and antidepressant medication for some disorders [1, 2]. Moreover, it is an acceptable intervention for pregnant women [3]. The adapted MBSR program will be referred to as prenatal MBSR.

Entering motherhood is one of the most intensive transitional stages in life that require adaptations on many levels [4], and this process is likely challenged by the simultaneous presence of psychosocial vulnerabilities. A history of any psychopathology or psychosocial adversities, including low social support and abuse, are predictors of mental disorders during and after pregnancy with little diagnostic specificity [5]. Stress and mental disorders in pregnancy have been associated with adverse outcomes such as preterm birth and/or low birth weight [6]. Moreover, it is an independent risk factor for later disruptions in child development including an increased risk for mental disorders [6, 7]. Mental disorders often have an early onset, compared to other chronic diseases, with about 50% starting before the age of 14 years and 75% before the age of 24 years [8]. From a societal perspective, early onset increases the years the individual is in need of support from health and welfare services. Consequently, reducing the risk of mental disorders is a crucial public health goal [8]. Evidence also  points to children experiencing multiple adversities in childhood having a markedly increased all-cause mortality risk in adulthood [9]. Outcomes from a meta-analysis on the effectiveness of interventions in mentally ill parents concluded that the risk of developing the same mental illness was reduced by 40% in the children [10]. This finding provides support for early intervention and prevention. The prenatal period is a sensitive period, and prevention of mental disorders during this time in psychosocially vulnerable pregnant women could possibly have a long-lasting impact for the benefit of both the individual, their families, and society [8].

Mindfulness can be conceptualized as an attentional skill [11], and the practice of mindfulness meditation is increasingly incorporated into mental health interventions [12]. MBSR was chosen as the “mother” program, because it is applicable to a broad range of conditions and contexts [12, 13]. It has a growing evidence base with meta-analyses consistently pointing to reductions in symptoms of stress, anxiety, and depression in both clinical and non-clinical populations [1, 14, 15]. MBSR was developed as an education and training vehicle for those suffering from chronic health problems and the mounting demands associated with psychological and emotional stress. The focus of MBSR is on learning how to relate to life challenges in new ways [16, 17]. One core feature of mindfulness meditation is the relationship between emotional suffering and the various strategies used to deal with it, e.g., distraction, repression, aggression, or somatic symptoms that may ultimately generate even more suffering [12]. One such maladaptive form of coping with emotional suffering is substance abuse. By training the capacity of becoming aware of one’s own mental state and developing a relationship with it can contribute to process suffering and ultimately improve mental health [11, 12]. In other words, the intention of mindfulness meditation training, in this context, is to engage and strengthen the pregnant women’s internal resources, thereby optimizing recovery or prevent relapse of mental health disorders during the perinatal period. Moreover, the intention of the training is also to teach skills that hold the potential to promote the formation of a healthy relationship with the child, i.e., present centered awareness and meta-awareness. When forming a deeper connection with oneself, a person is better able to connect with her/his child, and this quality of presence is at the heart of establishing a healthy bond.

More studies have addressed mental health in pregnancy using mindfulness-based interventions, e.g., MBSR; mindfulness-based cognitive therapy (MBCT); or mindfulness-based yoga. Systematic reviews and meta-analyses point towards a trend in favor of mindfulness-based interventions but state that shortcomings in study designs limit the conclusions. The majority of studies are pilot and feasibility trials that are not adequately powered to demonstrate the effectiveness [3, 18, 19]. A recent randomized controlled trial (RCT) examined the effect of a Mindfulness-Based Childbirth and Parenting Program (MBCP), which is adapted from MBSR [20], in pregnant women at risk of perinatal depression. The results of the study showed that MBCP significantly reduced perceived stress and depressive symptoms when compared to an active control group [20]. However, more research is needed to explore the possible benefits of mindfulness-based interventions on mental health in pregnancy, and in particular in psychosocially vulnerable groups [3, 19]. Moreover, none of the studies has included measures of mother-fetus relation such as prenatal reflective functioning. This measure may serve as an early indicator of mother-child interaction [21]. This is a relevant outcome to explore given the possible negative impact on the fetus and offspring of maternal mental disorders during pregnancy. Reflective functioning is the operationalization of mentalizing [22]. Mentalizing is a fundamental capacity in our social environment. It refers to the capacity to understand others and ourselves as motivated by intentional mental states, such as feelings, desires, wishes, goals, and attitudes [22]. It is not a unitary construct but covers both affective and cognitive components. Mindfulness is one such affective component involving the ability to attend to one’s own internal mental states [22]. Imbalance in mentalizing processes has been suggested as key to the understanding of psychopathology irrespective of diagnostic category [23]. In summary, more research on the effect of mindfulness-based interventions, on mental health, in the perinatal period is needed and in particular in psychosocially vulnerable groups.

### Study aim and objectives

The primary aim of the study is to determine the feasibility and acceptability of the prenatal MBSR program delivered to psychosocially vulnerable pregnant women in a hospital-based setting. The objectives are to examine the following: (1) acceptance of trial participation; (2) acceptance of allocated interventions; (3) risk of bias: loss to follow-up in the study arms, acceptance and compliance with the intervention, i.e., attending ≥ 5 sessions; and (4) the extent of missing data leading to missing outcomes. The secondary aim is to explore the potential efficacy of the prenatal MBSR program on self-reported measures of stress, well-being, anxiety, depression, reflective functioning, mindfulness, and self-compassion. The outcomes of the feasibility study will inform the design of a fully powered RCT.

## Methods/design

### Design

The protocol is for a randomized, single-center feasibility trial comparing the prenatal MBSR program as an add-on to usual care with usual care alone. Participants will be randomized in a 1:1 ratio to an intervention or waitlist control group. A completed SPIRIT checklist is available in Additional Files and the study flow is outlined in Fig. 1. Self-report measures will be collected at three time points: (1) at baseline prior to randomization, (2) immediately after completion of the prenatal MBSR program, and (3) 3 months post-completion. Participants in the waitlist control group will be offered participation in a MBSR program after completion of the study.

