### Recruitment and consent

Pregnant women referred to the outpatient clinic are recruited at their first or second consultation with a midwife. The first consultation is on average approximately 18 weeks’ gestation and the second approximately 24 weeks’ gestation. In order to determine eligibility, the midwife will use the information from the patient record regarding reasons for a referral to the outpatient clinic. The information includes past or present psychiatric diagnoses, and past or present substance abuse. The information is registered in an Excel sheet along with name and contact information and passed on to the responsible researcher. The midwife will provide verbal information about the study and email written information to eligible women, who express an interest in participating in the study. An online zoom interview is then scheduled with the responsible researcher. The women will be encouraged to find a time and a place where the interview can take place undisturbed, and information is provided about the possibility of having a partner or other person present. The online format provides the women with an opportunity to participate in the interview in their own homes as they may feel particularly vulnerable during the corona pandemic. The corona pandemic, coupled with our experience working with this population, led to offering this option. If an online interview is not possible, the interview will be conducted at the outpatient clinic. The interview will contain information about the study such as study criteria, procedures, randomization, intervention, and motivation for study participation. Women who consent to study participation will be asked to sign the consent form within 1 week from the interview. The women can choose to either return a signed consent form by email or sign the consent form at the outpatient clinic, who will then return it to the responsible researcher.

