### Inclusion and exclusion criteria

The aim of the study is to address prenatal mental care in psychosocially vulnerable women with no particular attention to any specific psychiatric diagnosis or other psychosocial vulnerability. However, there are some cases where MBSR is not suited, which is specified in the exclusion criteria.

The following are the inclusion criteria:
Estimated due date no sooner than 3 months from the start of the intervention. The adapted MBSR program includes nine weekly sessions, and these criteria were included in order for the women to be able to complete the intervention.Eighteen + years of age.Speak and write Danish.Available for group intervention scheduled sessions. Being unavailable for two or more sessions is a reason for exclusion from study participation.Written informed consent to study criteria.

The following are the exclusion criteria:
Concurrent substance abusePsychotic disorders and post-traumatic stress disorderSuicidality

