#### Prenatal Reflective Functioning Questionnaire

Parental reflective functioning refers to the caregiver’s capacity to reflect upon his/her own internal mental experiences as well as those of the child [34]. The Prenatal Parental Reflective Functioning Questionnaire (P-PRFQ) is a recently developed, 14-item questionnaire for assessing early parental mentalizing capacity [4]. Responses are rated on a scale from 7 “strongly agree” to 1 “strongly disagree.” The raw scores range from 14 to 98 and the index sum from 1 to 7. Higher scores indicate higher prenatal mentalizing capacity. The P-PRFQ has shown good initial psychometric properties [4].

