### Data analyses

Statistical analyses will be performed using SPSS for Windows (version 27; IBM Corp, Armonk, NY). Skewness, kurtosis, and visual inspection of normal Q-Q plots will be used to inspect normality. Descriptive statistics will be presented as mean and SDs or median and interquartile range (IQR) depending on the distribution of the continuous variables or as frequencies for categorical variables.

Recruitment, participation, and retention rates will be reported and presented in a CONSORT flow diagram [40]. Data collected on numbers of eligible participants recruited, numbers randomized, adherence to, and compliance with the intervention, as well as dropouts lost to follow-up, will be presented as percentages and used to inform the development of a full-scale RCT.

Acceptability of the intervention will be assessed by dropout rates, by computing the mean number of completed sessions, and time spent on at-home practices in the prenatal MBSR group. Participation in ≥ 5 sessions will be considered compliant with the program. A loss to 12-week follow-up analysis will be conducted for age, education, employment, history of a mental disorder, participation in < 5 sessions of the intervention, and pre-scores on the PSS-10 by means of t-test and chi-squared test (χ^2^). A loss to intervention analysis will be conducted for participants attending < 5 sessions of the intervention applying a similar approach.

Analyses of a possible effect of the intervention will be performed based on the intention-to-treat principle, meaning that all participants will be included in the analysis irrespective of their compliance with the intervention protocol. Lastly, an additional per-protocol analysis will be conducted. Since the study is not powered by formal hypothesis testing, only effect estimates and 95% CIs will be presented in accordance with the CONSORT criteria for reporting of feasibility or pilot studies [40].

Independent t-tests (or the non-parametric equivalent Mann-Whitney U) will be conducted to compare the pre- and post-questionnaire scores of the intervention and control groups. In case of skewed distributions in baseline variables, e.g., age and history of mental disorders, logistic regression analyses will be performed.

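### The schedule as written gives a prenatal reflective functioning questionnaire at a 3-month follow-up that most women will reach after giving birth

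*Protocol article*

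**What the plan says.** The Design section states: "Self-report measures will be collected at three time points: (1) at baseline prior to randomization". The other two time points are "2) immediately after completion of the prenatal MBSR program, and (3) 3 months post-completion". Below they are T1, T2 and T3. No instrument is excepted from any of them. The section Secondary feasibility outcome counts reflective functioning among the self-report outcomes and describes one questionnaire packet.

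The only instrument given for reflective functioning is the P-PRFQ, of which the protocol says: "Higher scores indicate higher prenatal mentalizing capacity". No postnatal version or substitute is named.

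Three other sections fix the timing:

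- Recruitment and consent: "The first consultation is on average approximately 18 weeks’ gestation and the second approximately 24 weeks’ gestation". An interview follows, and then: "Women who consent to study participation will be asked to sign the consent form within 1 week from the interview".
- Inclusion and exclusion criteria: "Estimated due date no sooner than 3 months from the start of the intervention". The reason given is that women should be able to finish the nine weekly sessions.
- Data analyses, which gives the follow-up in weeks: "A loss to 12-week follow-up analysis will be conducted".

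Baseline characteristics adds that the week of birth will be recorded. The program description offers online booster sessions at 3-month intervals after the program ends and invites mothers to bring their babies.

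**The concern.** The due-date criterion protects completion of the program, and with it T2. It does not reach T3, which comes another 3 months later. If most women have delivered by then, a questionnaire about mentalizing in pregnancy no longer fits them. They will leave it blank, or answer it in a way that cannot be compared with their pregnancy scores.

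Two things are at stake. The Background presents prenatal reflective functioning as a measure that earlier mindfulness studies in pregnancy did not include, so its scores should be interpretable. In addition, the fourth objective under Study aim and objectives is to learn how much outcome data goes missing. Gaps caused by an inapplicable form would be counted there as if they reflected participants' willingness to respond, and would be carried into planning of the full trial. No later analysis can recover prenatal scores from women who have already given birth.

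**Working it through.** The protocol gives no gestational age at T3, so there is no stated figure to reproduce. The check is timeline arithmetic.

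**Inputs from the protocol**

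- Gestation at recruitment: about 18 or 24 weeks. These are averages; no distribution is given.
- Program length *p*: nine weekly sessions, so 8 weeks from first to last session, or 9 calendar weeks.
- Follow-up *f*: 12 weeks (Data analyses) or 3 months, about 13 weeks (Design).
- Latest start: due date at least 3 months away, so 40 − 13 = week 27.

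**Assumptions, not in the protocol**

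- The due date is at 40 weeks.
- Control women are assessed on the same calendar as the program group.
- Gestation at birth is normal, with mean 39.5 and SD 1.7 weeks, or mean 40 and SD 2 weeks. Both were run to show a range.

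**Formulas**, for a start at week *s*

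- Gestation at T2 = *s* + *p*
- Gestation-equivalent at T3 = *s* + *p* + *f*
- Share delivered by T3 = Φ((*s* + *p* + *f* − mean)/SD)

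Example, start at week 20. The low end is 20 + 8 + 12 = 40, and with mean 40 and SD 2 the share is Φ(0) = 50%. The high end is 20 + 9 + 13 = 42, and with mean 39.5 and SD 1.7 the share is Φ(2.5/1.7), about 93%.

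| Start (week) | T2 (week) | T3 (week) | Delivered by T3 (assumed birth timing) |
|---|---|---|---|
| 18 | 26–27 | 38–40 | 16–62% |
| 20 | 28–29 | 40–42 | 50–93% |
| 22 | 30–31 | 42–44 | 84–100% |
| 24 | 32–33 | 44–46 | 98–100% |
| 27 | 35–36 | 47–49 | about 100% |

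**Averaged over evenly spread start weeks**

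| Range of starts | Delivered by T3 |
|---|---|
| 18–24 | 64–93% |
| 18–27 | 76–95% |
| 20–27 | 89–99% |

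Of 60 women, 76% to 95% is 0.76 × 60 ≈ 46 to 0.95 × 60 = 57. That leaves about 14 down to 3 women still pregnant at T3, before any loss to follow-up.

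T2 falls at about weeks 26 to 36. Even for the latest allowed start, about 2% or fewer would have delivered by then. The P-PRFQ is therefore usable at T1 and T2, and the problem is confined to T3.

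**The case against.** Several points on the other side have weight.

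- *The P-PRFQ at T3 is inferred.* The Design sentence names no instrument, the flow figure could not be read here, and a journal article commonly leaves the visit-by-instrument table to the full protocol. This is fair as a caution. The sentence is nevertheless unqualified, and nothing visible excepts the P-PRFQ or names a postnatal substitute.
- *Women who start early may still be pregnant.* This stands. A reader might infer that almost every woman will have delivered, or that nobody could validly answer at T3. The documents do not support that: at a week-18 start, 38% to 84% could still be pregnant. How many women start that early depends on the wait between consultation and group start, which is not given.
- *The other scales are suitable after birth.* This stands too. A reader might extend the criticism to every T3 measure. However, the protocol reports that the EDS is validated before and after birth and that the DASS leaves out somatic items that may mislead in either period. The Background speaks of the perinatal period, so a follow-up after birth is within scope.
- *No analysis separates pregnant from postpartum responses.* That is true of the text shown, but the text sets out no effect analysis specific to T3, and such detail may sit in an analysis plan not at hand. Its absence is not a fault in this document.
- *Randomization should balance birth timing.* Agreed. Mixed timing mainly adds noise and is unlikely to bias the comparison between arms.

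**Conclusion.** The point holds for one instrument at one visit. As written, the Design section puts a pregnancy questionnaire at a time when most women will have given birth: about weeks 38 to 49 in gestation-equivalent terms, or from 2 weeks before the due date to 9 weeks after it.

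The week ranges follow from the protocol's own figures plus a 40-week due date. The percentages also rest on the assumed birth-timing distributions and on evenly spread starts. The word *most* is supported under every range of starts in the table of averages; a share close to 100% is supported only for starts from about week 24.

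The consequences are P-PRFQ scores at T3 that are absent or cannot be interpreted for most women, and an overstated missing-data rate. The other scales are unaffected as to validity. The trial is an unpowered feasibility study and this outcome is secondary and exploratory, so the correction is of moderate importance and should not be treated as a condition for the trial's validity.

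**What to change.** 1. State which instruments are collected at T3. Remove the P-PRFQ from that packet and make T2 its post-baseline time point. Alternatively, replace it at T3 with a postnatal measure reported as a separate outcome and not pooled with the prenatal scores.
2. State that the absence of the P-PRFQ at T3 is by design and does not count towards the missing-data objective.
3. Use the week-of-birth data already planned to report, by arm, how many women were pregnant at T3 and the weeks since birth for the rest. Keep this descriptive. Birth timing is observed after randomization, and the Background itself links stress to preterm birth, so adjusting the T3 comparison for it could distort the effect estimate.
4. Label T3 results as late pregnancy or early postpartum.

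The cost is a change to the REDCap packet and a few lines of text. The T3 questionnaire becomes 14 items shorter if the P-PRFQ is dropped without replacement. What is given up is one P-PRFQ time point, including scores from the minority still pregnant at T3.
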